Conventional ways of assessing drug adherence include blood drug level measurement, pill counts, patient interview/use of questionnaires, and electronic monitoring. Blood drug concentration provides direct evidence, but is rarely useful due to inter-individual variability in pharmacodynamics [6]. There is also risk of errors due to the white-coat compliance where drug adherence improves abruptly for the 5 days immediately preceding a physician visit [7]. Pill count is even less reliable, barely providing information on dosing time compliance. While easy to implement, patient interview/questionnaires also pose reliability issues. Electronic monitoring has been regarded as the standard assessment of adherence [8]. It keeps records of the date/time when patients open the pill box, and the computer-connected data is downloadable and analyzable. Though the simple date/time data does not really ensure whether medication is actually taken, electronic monitoring is still considered the most reliable [9]. Henriksson et al. have conducted a study where the date/time record of immunosuppression administration in KTRs was transmitted via web-based reporting tools. Subjects were randomized to the electronic adherence monitoring system or the control system. The prospective study with 1-year follow-up has demonstrated a greater adherence with a lower rejection rate in the electronic monitoring group than in the control group [10]. In a more recent randomized clinical trial, Reese et al. have investigated KTRs who had been given pill bottles to demonstrate that the greatest adherence was achieved in those who received provider notification together with customized reminders [11].

The present clinical trial aims to investigate efficacy and stability of continuous adherence management in KTRs by means of an information and communication technology (ICT)-based centralized clinical trial monitoring system.

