### Study design

This study has a multicenter, open-label, prospective, randomized controlled trial (RCT) design. One hundred fourteen KTRs who fill out the Informed Consent Form are registered and randomized 1:1 into the ICT-based centralized clinical trial monitoring group (*n* = 57) or the ambulatory follow-up group (*n* = 57). The planned follow-up duration is 6 months (Fig. 1). The ICT-based centralized clinical trial monitoring group is given a smart pill box equipped with a personal identification system. Fingerprint registration is required in advance, so that it would be used for authentication before each use of the smart pill box later. The adherence-related information obtained from the pill box is saved, monitored, and sent out via a home monitoring system. Of the home monitoring system data, those necessary for the clinical trial are extracted and incorporated into the electronic Case Report Form (eCRF) system. All data is consolidated and managed within the comprehensive clinical trial management system (CTMS). In the ICT-based, centralized clinical trial monitoring group, feedback is sent to both patients and medical staff in the form of texts and pill box alarms if there is a dosage/dosing time error or a missed dose.

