**Fig. 1 Fig1:**
[figure not shown]
ICT-based study design. *ICT* information and communication technology, *R* randomization, *S* screening, *W* week

Both groups are to make six office visits after randomization at 4, 8, 12, 16, 20, and 24 weeks. Each visit requires measurement of blood drug level, creatinine level, and estimated glomerular filtration rate (eGFR). Serum BK virus is assessed at 12 weeks, and panel reactive antibody (PRA) at 24 weeks. Both groups keep a drug administration diary that specifies date, whether a dose is taken or not, dosing time, and dosage. At each visit, subjects go over the diary with investigators and fill out a questionnaire using the Modified Morisky Adherence Scale [12]. The ICT-based centralized clinical trial monitoring group completes a patient Satisfaction Questionnaire developed by the ICT Clinical Trial Support Center at 4 and 24 weeks. The system Satisfaction Questionnaire can be found in Additional file 1. The protocol flow is shown in detail in the Standard Protocol Items: Recommendations for Interventional Trials (SPIRIT) figure in Fig. 2. A SPIRIT Checklist is provided in an Additional file 2.

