### Sample size

We hypothesized that the ICT-based centralized monitoring group would be superior to the control group in terms of dose-taking compliance. A one-tailed test with a 0.05 significance level and 80% power provided a size of 51 in each group. With an estimated 10% dropout, the final sample size of 57 was determined (a total of 114 subjects, 57 in each group).

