### Primary outcomes

The primary outcome in this trial is adherence to medication. Both in the ICT-based centralized clinical trial monitoring group and the control, pill counts are done at 4, 8, 12, 16, 20, and 24 weeks of follow-up. Multiple items of adherence – dose-taking compliance, dose-frequency compliance, dose-interval compliance, and drug holidays – are assessed based on the smart pill box data in the ICT-based centralized monitoring group and the drug administration diary in the ambulatory follow-up group, respectively. In the ICT-based centralized monitoring group, three types of immunosuppressants—tacrolimus, mycophenolic acid, and steroids—are placed in a single bag, which is then placed inside a smart pill box. The patient’s medication usage is assessed based on the perceived weight of the leftover medications in the bag. On the basis of this weight information, we can identify the type and dose of medications that the patient has ingested, and calculate the adherence. Each item of adherence is listed below [15]:Dose-taking compliance = the number of pills taken over a certain time period/the number of pills prescribed over the same period × 100%Dose-frequency compliance = the number of days of correct daily dosing frequency over a certain time period/the number of days over the same period × 100%Dose-interval compliance: the number of correct dosing interval over a certain time period/the number of days over the same period × 100%.A correct dosing interval is defined with a ± 25% margin (in this trial, medication is taken twice a day, with a dosing interval of 12 h. Allowed dosing interval is thus ranged from 9 to 15 h)Drug holidays = the number of days without dose taking/the number of days over the same period × 100%Medication possession ratio = the sum of the days’ supply for all fills of a given drug in a particular time period/the number of days in the time period × 100%

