### Secondary outcomes

The secondary outcomes in this trial include blood drug levels, immunological outcome, clinical outcome, patient satisfaction with the system, and the system stability and cost-effectiveness. The trough levels of tacrolimus and mycophenolic acid, creatinine level, and eGFR are measured at 4, 8, 12, 16, 20, and 24 weeks of follow-up. PRA is assessed at baseline and 24 weeks, and serum BK virus at 12 weeks. For clinical outcome evaluation, biopsy-proven acute rejection (BPAR) and graft loss developing during the follow-up are monitored. The patient Satisfaction Questionnaire is filled out at 4 and 24 weeks in the ICT-based centralized clinical trial monitoring group in order to assess how well the patients are satisfied with the system-enabled adherence management. The malfunction rate of the ICT-based centralized monitoring system is checked as well as any discrepancy between the smart pill box record and the patient-kept drug administration diary. Information about patients’ medication use sent to the ICT-based monitoring system is compared with the daily records of medication use written by the patients (type of medications used, number of pills ingested, and time of ingestion) to assess how closely they match. Stability is measured by using the following equation:$$ \frac{\mathrm{Number}\  \mathrm{of}\  \mathrm{pills}\  \mathrm{taken}\  \mathrm{over}\ \mathrm{a}\ \mathrm{certain}\  \mathrm{period}\  \mathrm{according}\  \mathrm{to}\  \mathrm{the}\ \mathrm{ICT}\hbox{-} \mathrm{based}\  \mathrm{centralized}\  \mathrm{monitoring}\  \mathrm{system}}{\mathrm{Number}\  \mathrm{of}\  \mathrm{pills}\  \mathrm{prescribed}\  \mathrm{over}\  \mathrm{the}\  \mathrm{sampling}\  \mathrm{period}\  \mathrm{according}\  \mathrm{to}\  \mathrm{the}\  \mathrm{daily}\  \mathrm{record}\  \mathrm{of}\  \mathrm{medication}\ \mathrm{use}}\times 100\%. $$

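### Four primary adherence items are read from the smart pill box in one arm and from the patient's diary in the other, so the group difference includes any difference between the two instruments

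*Protocol article*

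**What the plan says.** The Primary outcomes section opens with "The primary outcome in this trial is adherence to medication". It names four items (dose-taking compliance, dose-frequency compliance, dose-interval compliance and drug holidays) and says that they are assessed "based on the smart pill box data in the ICT-based centralized monitoring group and the drug administration diary in the ambulatory follow-up group". Sample size shows which item the trial was sized on: the hypothesis is that "the ICT-based centralized monitoring group would be superior to the control group in terms of dose-taking compliance". Statistical analysis compares adherence between groups with a t test and mentions no allowance for the source of the data.

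The box is described for one arm only: "The ICT-based centralized clinical trial monitoring group is given a smart pill box equipped with a personal identification system". Two other records exist in both arms. Study design says: "Both groups keep a drug administration diary that specifies date, whether a dose is taken or not, dosing time, and dosage". Primary outcomes says that in both groups "pill counts are done at 4, 8, 12, 16, 20, and 24 weeks of follow-up", but not which adherence item these counts supply. Secondary outcomes includes a check of "any discrepancy between the smart pill box record and the patient-kept drug administration diary", placed with system malfunction and stability. The limitations in the Discussion do not mention the difference in source.

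**The concern.** A difference in measurement that coincides exactly with treatment arm is not balanced by randomisation and does not shrink with sample size. The box infers intake from the weight left in the bag. The diary is what the patient writes down. Each can err in its own way: a patient may record doses that were not taken or leave entries out, and a bag may lose weight without its contents being swallowed. The article itself concedes in the Background that electronic records do not prove ingestion.

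At stake is the headline result. If the diary reads high relative to the box, a real gain from the monitoring system is diluted or lost. If the box reads high relative to the diary, a gain can appear where there is none. Nothing in the planned comparison separates these possibilities from a true effect.

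**Working it through.** **Step 1. Where the numbers come from.** From Sample size: one-tailed 0.05, 80% power, 51 per group, 10% dropout, 57 per group. The article gives no effect size, no SD and no box-diary difference, so these are assumed below.

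**Step 2. The plan's own figure.** The dropout step reproduces: 51/0.90 = 56.7, rounded up to 57 per group and 114 in total. The 51 cannot be derived without an effect size, but it can be solved backwards:

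d = (z0.95 + z0.80) × √(2/51) = (1.645 + 0.842) × 0.198 = 0.492.

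With d = 0.5 an exact one-sided t test has power 0.799 at 50 per group and 0.806 at 51. So 51 is the first size to reach 80%, and d = 0.5 is a reasonable working assumption.

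**Step 3. What the comparison estimates.** Let δ be the true difference in adherence (ICT minus control), e_box the mean error of the box in the ICT arm and e_diary the mean error of the diary in the control arm. The planned contrast has expectation

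δ + (e_box − e_diary).

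The bracket is zero only if the two instruments have the same mean error. In the arm-by-arm data as assigned, δ and the bracket cannot be estimated separately.

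**Step 4. Size, as an illustration.** Take a constant gap of 2 percentage points and write b = 2/SD for the gap in SD units. With 51 per arm there are 100 degrees of freedom, the one-sided critical value is 1.660 and √(51/2) = 5.05. The non-centrality is (0.5 − b) × 5.05 if the diary reads high and the true effect is 0.5 SD, and b × 5.05 if the box reads high and there is no true effect.

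| Assumed SD (points) | True effect at d = 0.5 (points) | b | Power if diary reads 2 points high | Type I error if box reads 2 points high |
|---|---|---|---|---|
| no gap | – | 0 | 0.81 | 0.05 |
| 5 | 2.5 | 0.4 | 0.13 | 0.64 |
| 10 | 5 | 0.2 | 0.44 | 0.26 |
| 20 | 10 | 0.1 | 0.64 | 0.13 |

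For example, at SD 10 the non-centrality is (0.5 − 0.2) × 5.05 = 1.51 in the power column (0.44) and 0.2 × 5.05 = 1.01 in the type I error column (0.26).

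**Step 5. Is a common instrument available?** The diary is kept in both arms and covers intake, time and dosage, so it can supply all four items. The visit pill count is also done in both arms and can supply dose-taking compliance, which is pills taken over pills prescribed. One caution applies: the article's list of components and information to be collected includes remaining pill counts among the box data. It does not say whether the ICT-arm visit counts are made by hand. If they are box readings, a pill-count comparison carries the same problem.

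**The case against.** The strongest defence is that pill counts in both arms sit under Primary outcomes and that the dose-taking formula suits them, so a like-for-like measure may be intended. That has some force: the article does not state what the counts are for, and a reader should not infer that a pill-count comparison was ruled out. But the sentence that follows ties dose-taking compliance, with the other three items, to box or diary. At best the text leaves two unreconciled sources for the item on which the trial was sized.

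Several stronger readings are tempting and are not supported:

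- **That every adherence item is affected.** Only four are assigned to box or diary. Medication possession ratio is listed too, with no source given.
- **That the article ranks the diary as unreliable.** The Background says "Electronic monitoring has been regarded as the standard assessment of adherence" and raises reliability problems with interviews and questionnaires. It does not mention diaries, and investigators go over the diary with the patient at each visit.
- **That the planned box-diary check shows a difference is expected.** It is an agreement check for system stability and predicts nothing about the result.
- **That the primary question cannot be answered at all.** If the diary over-reports and the box does not, the bias runs against the ICT arm and a significant benefit would be conservative. Only net bias towards the box undermines a positive result. The documents do not say which case applies.

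It is also fair to object that the figures rest on assumptions. A constant shift ignores the ceiling at full adherence: if control adherence is already high, a large diary inflation may be impossible. The range of SDs with a modest gap is given for that reason.

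The agreement check does not rescue the comparison. It is made in the ICT arm only, where patients receive alarms and texts that may change what they write, and no use of it in the primary analysis is stated.

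**Conclusion.** The point holds for the four named items. Measurement source and arm are fully confounded in the primary comparison, and nothing else in the article resolves it. This conclusion depends on no assumed value.

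The size is unknown. Under the assumptions in the table, a gap of only 2 points is enough to cost much of the power or to lift the type I error well above 0.05, and the effect is larger when the SD is smaller. These figures are arithmetic on an assumed effect, SD and constant gap. They are not evidence of how far box and diary differ in this trial. Because the problem lies in the primary outcome and can move the result either way, it should be corrected before the groups are compared.

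**What to change.** Amend Primary outcomes so that each between-group adherence comparison uses one instrument collected the same way in both arms:

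- **Dose-taking compliance:** the visit pill count, provided ICT-arm counts are made by hand as in the control arm and not read from the box. State this explicitly. If it cannot be met, use the diary in both arms.
- **Dose-frequency compliance, dose-interval compliance and drug holidays:** the diary in both arms.
- **Smart pill box data:** report within the ICT arm, with the box-versus-diary comparison already planned under Secondary outcomes, to describe diary error in that arm.

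Both records are already planned for both arms, so the change is mainly to wording and analysis, unless hand counts have to be introduced in the ICT arm. It has real costs. By the article's own account electronic monitoring is the more reliable measure and pill counts are less so; a patient-kept diary is also likely to be weaker than the box. The trial is open-label and only ICT patients receive alarms, so diary reporting may still differ by arm. A shared instrument removes the box-diary confounding but does not guarantee equal error. The unstated SD and effect behind 51 per group may also not carry over to the new measure, so the sample size should be rechecked against it.

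### Dose-interval compliance counts intervals in the numerator and days in the denominator; with twice-daily dosing, perfect timing scores about 200%

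*Protocol article*

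**What the plan says.** The Primary outcomes section of the protocol article names the adherence items to be assessed as "dose-taking compliance, dose-frequency compliance, dose-interval compliance, and drug holidays", and then gives a formula for each. Three statements matter here.

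- Dose-interval compliance is "the number of correct dosing interval over a certain time period/the number of days over the same period", times 100%.
- The dosing pattern is fixed in the same item: "in this trial, medication is taken twice a day, with a dosing interval of 12 h".
- The tolerance is also given: "A correct dosing interval is defined with a ± 25% margin", and "Allowed dosing interval is thus ranged from 9 to 15 h".

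The formula directly before it, for dose-frequency compliance, has days both above and below the line: "the number of days of correct daily dosing frequency over a certain time period/the number of days over the same period × 100"%.

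The Statistical analysis section compares adherence between groups with a t test and promises mean, SD, median, minimum and maximum for measurements at each visit. The Sample size section states its hypothesis for dose-taking compliance.

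**The concern.** A compliance percentage should reach 100% when everything is done as prescribed. Here the numerator is a count of intervals and the denominator a count of days, and on the article's own account there are about two intervals in a day. Nothing in the article caps the result, rescales it or redefines the numerator as days.

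At stake is the meaning of the reported numbers. Applied literally, the visit tables would show maxima near 200%. A group mean of 100%, which most readers would take as perfect timing, would describe patients whose intervals were wrong about half the time. Someone who notices the mismatch during analysis must also choose a repair, and the text does not say which of two different measures was meant. In an open-label trial, the definition of a primary-outcome item is better not settled after the data have been seen.

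**Working it through.** **Inputs, all from the protocol article.** Two doses a day, 12 h apart, with a ±25% margin (Primary outcomes). Visits every 4 weeks to week 24 (Study design), so a visit period is D = 28 days and the whole follow-up is D = 168 days.

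**The article's own figure.** 12 × 0.75 = 9 h and 12 × 1.25 = 15 h. The allowed range is reproduced exactly.

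**Number of intervals.** D days at two doses a day give 2D doses. They enclose 2D − 1 intervals, or 2D if the interval from the last dose before the period is counted.

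**Score under the stated formula**, correct intervals / D × 100%:

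| Period | Intervals | All correct | Half correct |
|---|---|---|---|
| 28 days | 55 | 55/28 = 196.4% | 27.5/28 = 98.2% |
| 28 days | 56 | 56/28 = 200.0% | 28/28 = 100.0% |
| 168 days | 335 | 335/168 = 199.4% | 167.5/168 = 99.7% |
| 168 days | 336 | 336/168 = 200.0% | 168/168 = 100.0% |

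A score of exactly 100% over 168 days needs 168 correct intervals, which is 168/335 = 50.1% of them.

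**Effect on a group difference.** Take illustrative true levels of 90% and 75% of intervals correct over 168 days. The stated formula gives 0.90 × 335/168 = 179.5% and 0.75 × 335/168 = 149.6%. The difference appears as 29.9 points where the true one is 15.

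**Effect on the test.** If every value is multiplied by the same constant k, the difference and its standard error are both multiplied by k, so t does not change. Ranks do not change either, so the Mann-Whitney result also stands. Here k lies between 1.96 and 2.00, depending on period length and the counting convention, so the test is essentially unchanged.

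**Do the two possible repairs agree?** Take 28 days and 56 prescribed intervals, and assign each interval to the day on which it ends. Suppose, for illustration only, that seven doses on well-separated days are each taken 4 h late. Each makes one interval 16 h and the next 8 h. Both are outside 9 to 15 h, so 14 intervals are wrong and 56 − 14 = 42 are correct.

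- As written: 42/28 = 150%.
- Correct intervals over prescribed intervals: 42/56 = 75%.
- Days with all intervals correct over days, if the late doses are morning doses: both wrong intervals end on the same day, 7 days are spoiled, and the score is 21/28 = 75%.
- The same measure, if they are evening doses: the wrong intervals end on two different days, 14 days are spoiled, and the score is 14/28 = 50%.

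The two repairs are therefore not constant multiples of each other, and the choice between them can alter a comparison.

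**The case against.** The strongest reply is that this is a slip of wording with little consequence.

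- **A missing phrase may explain it.** The numerator is ungrammatical and follows a formula that counts days over days. If the authors meant days of correct dosing interval, the denominator is right and the maximum is 100%. This is plausible, and the article does not settle it. It stands as a reason not to assume that the denominator is the faulty part, and not to claim that the data will in fact be mis-scaled by two. It does not rescue the formula as printed.
- **The comparison survives.** A near-constant factor in both arms leaves the t test essentially as it was, and the article sets no cut-off on this item that would misclassify patients. This stands.
- **The powered item is a different one.** The sample size rests on dose-taking compliance, whose formula is pills over pills. This stands too.

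A reader might infer that the primary comparison is biased or the trial mis-sized. The last two points show that the document supports neither. A reader might also infer that this is the only item that departs from a common scale topping out at 100%. That is not so. Correct use scores 0% on drug holidays, medication possession ratio can exceed 100% with early fills, and dose-taking compliance can exceed 100% with overuse. The fair comparison is only with dose-taking and dose-frequency compliance, where 100% is what correct use scores.

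**Conclusion.** The definition is wrong as printed, because its numerator and denominator are in different units. Taken literally, full compliance scores 196% to 200%, about half the intervals correct scores about 100%, and reported values and absolute group differences are about twice what they should be. This is a fault of definition and reporting scale in one of several primary-outcome items. It does not by itself distort the P value, the direction of effect or the sample size.

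The factor of two assumes twice-daily dosing for every patient, as the article states. A drug taken once a day would not show it. That the test is unaffected assumes that the printed formula is applied uniformly. It does not cover a repair chosen during analysis, because the two candidate repairs can rank patients differently.

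**What to change.** Before analysis, make the units match and state which measure is meant:

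1. **Share of intervals:** correct intervals divided by prescribed dosing intervals in the period. That is 2 × days, or 2 × days − 1 if the interval from the last earlier dose is not counted; say which. The denominator should be prescribed rather than observed intervals, because a missed dose merges two intervals into one and would otherwise shrink the denominator.
2. **Share of days**, if days were intended: days on which all intervals were correct, divided by days. State to which day an interval that spans midnight belongs.

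Either version runs from 0 to 100%. The cost is a one-line correction to the definition and to the derivation of the variable. No new data are needed, and the sample size is untouched.

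### The 9–15 h window for a correct dosing interval rests on a twice-daily premise that the eligibility criteria do not secure, and the scoring unit and denominator need fixing with it

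*Protocol article*

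**What the plan says.** In the protocol article, Primary outcomes lists the adherence items as "dose-taking compliance, dose-frequency compliance, dose-interval compliance, and drug holidays". A correct dosing interval is one within ±25% of the interval. The text then applies this to a single schedule: "in this trial, medication is taken twice a day, with a dosing interval of 12 h". It concludes: "Allowed dosing interval is thus ranged from 9 to 15 h". The score is "the number of correct dosing interval over a certain time period/the number of days over the same period", expressed as a percentage.

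In the monitored arm the three drugs "are placed in a single bag, which is then placed inside a smart pill box". The same section says that from the weight "we can identify the type and dose of medications that the patient has ingested, and calculate the adherence". Control patients are scored from their diary.

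Study participants requires that patients take tacrolimus, mycophenolic acid and steroids. It sets no frequency or formulation for any of them, and no listed exclusion removes a once-daily schedule.

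Smart pill box states that the device checks intake against a prescribed schedule and holds a database of such schedules.

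**The concern.** A tolerance defined as a percentage of the interval can follow whatever schedule a patient has been prescribed. Once converted to a fixed number of hours, it is valid only for the schedule used in the conversion. Here that is 12 h, stated once for all medication and not by drug. Nothing in the eligibility criteria ensures that every drug of every patient follows it.

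The neighbouring items do follow the prescription: dose-taking compliance divides by pills prescribed, and dose-frequency compliance counts days on which the daily frequency was correct. Only the interval item is tied to one assumed schedule.

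For a drug on another schedule, the interval score would reflect the prescription and not the patient's behaviour. The size of the effect depends on whether intervals are scored by drug or by dosing event (each opening of the shared bag, or each diary entry time). The article does not say which, and its two measurement sources could be handled differently.

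**Working it through.** **Inputs.** Margin ±25%, interval 12 h, window 9–15 h, and the formula of correct intervals over days (all Primary outcomes). Follow-up is 24 weeks (Study design) = 168 days. The 24-h drug is an assumption used for testing; the documents mention none.

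**1. The plan's own figure.** 12 × 0.75 = 9 h and 12 × 1.25 = 15 h. The stated window is reproduced exactly.

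**2. Perfect intake, scored drug by drug, 9–15 h window.**
- 12-h drug: 2 × 168 = 336 doses, 335 intervals of 12 h, 335 correct.
- 24-h drug: 168 doses, 167 intervals of 24 h, 0 correct. The score is 0% with either denominator.

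**3. Fully adherent patient with two 12-h drugs and one 24-h drug.** Correct intervals as a share of all intervals:

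| Scoring unit | Calculation | Score |
|---|---|---|
| Dosing event, 24-h drug taken with a 12-h dose | 335/335 | 100% |
| Drug level, intervals pooled | (335 + 335 + 0)/(335 + 335 + 167) = 670/837 | 80.0% |
| Drug level, mean of three scores | (100 + 100 + 0)/3 | 66.7% |

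If the 24-h drug is taken as a separate event, it splits a 12-h gap. Taken 2 h after a dose it gives 335/503 = 66.6%; taken 5 h after, 167/503 = 33.2%. The patient's score is 0% only if all three drugs are on a 24-h schedule, or if the 24-h drug's score is reported alone.

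**4. The document's ±25% applied to the prescribed interval.** For 24 h: 24 × 0.75 = 18 h and 24 × 1.25 = 30 h. The 24-h drug then has 167 of 167 intervals correct. The 12-h drug keeps 9–15 h and 335 of 335.

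**5. The denominator.** Dividing by days as written, a perfectly taken 12-h drug scores 335/168 = 199.4%. Under the scaled window a perfectly taken 24-h drug scores 167/168 = 99.4%. Changing the window alone would therefore leave a factor of about two between schedules. Dividing by prescribed intervals gives 335/335 and 167/167, both 100%.

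**6. Effect on the arm comparison.** With a common scoring unit, the shift in the mean difference is the between-arm difference in the share of affected patients times the loss per affected patient. For one 24-h drug of three, that loss is 0 points (dosing event, taken together), about 20 points (pooled) or 33.3 points (mean of drugs). The share is not given, so no figure for the trial follows. If the monitored arm were scored by dosing event and controls by drug, the same perfect behaviour would score 100% against 66.7–80.0%, a gap of 20 to 33 points per affected patient in favour of the monitored arm.

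**The case against.** The strongest reply is that the article states twice-daily dosing as a fact of this trial. Silence on frequency in the eligibility list is not a contradiction, and regimen detail may sit in a full protocol that is not shown. This stands as far as it goes: the documents do not establish that anyone takes a drug every 24 h. A reader might infer from general practice that one of the three drugs is the likely candidate, but nothing in the text supports naming one. What remains is that the endpoint's premise and the eligibility list are not tied together.

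A second reply is that the general ±25% rule is already there and 9–15 h is only its application to 12 h. That is a fair reading of the intent, but the text then gives one allowed window and no other.

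A third is that a shared bag points to scoring by dosing event, where a once-daily drug taken with a twice-daily dose costs nothing. This is possible. The claim that drug type can be identified from weight makes drug-level scoring equally possible, and the text does not choose.

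Finally, the sample size rests on the hypothesis that the monitored group "would be superior to the control group in terms of dose-taking compliance", which this issue does not touch.

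**Conclusion.** The point holds conditionally and is of low severity. The 9–15 h window is correct arithmetic for a 12-h interval, but eligibility does not secure that interval. If a drug is prescribed every 24 h, it scores 0% at drug level under perfect adherence.

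Two stronger readings are tempting and should not be drawn:
- **That a fully adherent patient with one once-daily drug scores 0%.** With the other two drugs at 12 h, the score runs from no loss to 80.0% or 66.7%, and falls lower only if the once-daily drug is a separate dosing event.
- **That the arm comparison is biased.** The window is the same for both arms, and 1:1 randomisation gives no expected difference in regimens, provided both arms are scored by the same unit. Chance imbalance is possible, but its size cannot be derived from the documents.

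The day denominator is a separate defect in the same definition. It needs no assumption about regimens: a perfectly taken 12-h schedule scores 199.4%.

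These figures assume exact intake over 168 days. Dose-interval compliance is one of several primary items, and the hypothesis used for the sample size does not depend on it.

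**What to change.** 1. Reconcile Study participants and Primary outcomes on the twice-a-day statement, without changing any prescription. If every enrolled regimen is covered by it, say so.
2. Define a correct interval as within ±25% of the interval prescribed for that drug at that time. Take the schedule from the pill box database in the monitored arm and from the prescription record in controls. A 12-h drug keeps 9–15 h.
3. State one scoring unit, drug or dosing event, and use it in both arms. If dosing events are chosen, the reference interval is the scheduled gap between consecutive events.
4. Divide by the number of prescribed intervals instead of days, so that perfect adherence scores 100% under any schedule.

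The cost is a change to the endpoint wording and one prescribed-interval variable per drug. The monitored arm's schedules are already held in the box; control schedules have to be taken from prescriptions. No extra visits or patients are needed.
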